### Protocol for pedometer-only and control families

Following the baseline assessment, families allocated to the pedometer-only arm will be mailed pedometers and generic family PA promotion information produced by Walk4Life, a sub-brand of Change4Life (www.nhs.uk/change4life). Information will continue to be emailed to families (pedometer-only and FRESH arm families) fortnightly on four occasions. The information will provide families with tips to get walking daily and games that can be played while walking. Control families will be asked to carry on as normal and will not receive access to the intervention website, pedometers or any generic information.

### Outcome evaluation measures

Table 2 outlines the measures taken, including assessment order and estimated duration. Data collection will be carried out by two trained research staff and will occur in participating families’ homes (or an alternative location by arrangement). Outcomes will be assessed at baseline (prior to randomisation; spring/summer 2018), 8 weeks postbaseline (summer/autumn 2018) and follow-up (52 weeks postbaseline; spring/summer 2019) on all consenting family members (excluding children≤2 years).

**Table 2 T2:** Order of measures and estimated duration of data collection*†

Measure	Duration
1. Anthropometric measures (height, weight and waist circumference)	5 min/person
2. Questionnaire	20 min/family
3. Blood pressure‡	10 min/person
4. Step test (aerobic fitness)	Prep: 5 min/person Test: 10 min/family
5. Accelerometer and GPS explanation	5 min/family
6. Fictional Family Holiday (family functioning)	10 min/family
**Total duration of baseline measurement session (includes consent/assent process**)	**120** **min**
**Total duration of subsequent measurement sessions**	**105** **min**

*This table has been adapted from our feasibility study.

†Estimate based on a four-person household, total time increases by ~30 min per additional family member.

‡Duration is halved when calculating total duration because multiple monitors will be used to enable two family members to be measured simultaneously.

GPS, global positioning system.

### Primary outcome

#### PA outcomes

To assess PA, participants will be asked to simultaneously wear an ActiGraph GT3X+ triaxial accelerometer (ActiGraph LLC; Pensacola, Florida, USA) and QStarz Travel Recorder BT1000X GPS monitor (QStarz; Taipei, Taiwan). The accelerometer will be initialised to record data at a sampling rate of 50 Hz, while the GPS will be set to record a location every 10 s. The devices will be worn on each hip during waking hours for 7 consecutive days. A valid week will be defined as a minimum of 420 min/day from 3 days over the 7-day measurement period; however, this definition may be altered depending on participant compliance. Non-wear will be defined as ≥90 min consecutive zeros using the vector magnitude. Raw accelerometer counts will be downloaded and integrated into 5 s epochs. Evenson *et al* cut-points^36^ have been recommended to estimate PA intensity in youth^37 38^ and Troiano *et al*
39 cut-points for adults; these cut-points will be used in this study. In addition, family co-participation in PA will be measured by matching accelerometer and GPS data using Java. Novel methodological work will be completed to compute minutes of PA per day when family members are together at a given location from the matched data.

### Secondary outcomes

#### Health outcomes

Aerobic fitness will be measured using an 8 min submaximal step test (with 2 min rest), which provides an individual calibration of heart rate to work rate (energy expenditure per unit time) to predict a fitness estimate of a participants’ heart rate recovery index.^40^ Children<7 years will be excluded from the aerobic fitness test.

Height and weight will be measured once with a Leicester portable stadiometer and Seca 877 digital scale, respectively. Waist circumference will be measured twice, using a non-elastic tape measure. A third measure is taken if the first two measures differed by ≥3 cm. Body mass index will be calculated, and converted into age-specific and sex-specific percentiles using standard growth charts for children.^41^

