### Trial design

FRESH is a three-armed, parallel-group, randomised controlled pilot trial using a 1:1:1 allocation ratio with follow-up assessments at 8 and 52 weeks postbaseline (see figure 1). Following baseline assessment, families will be randomly allocated to one of three arms: (1) FRESH arm; (2) pedometer-only arm or (3) no-intervention control arm. All family members in the pedometer-only and FRESH arms receive pedometers and generic family PA promotion information. FRESH families additionally receive access to the intervention website. Control families will be asked to carry on as normal.

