### Participants

Families are deemed eligible to participate in this study if there is consent from at least one child in school Years 3–6 (aged 7–11 years, hereafter referred to as the index child) and at least one adult responsible for the index child. The adult must live with the index child in the main household (ie, the index child’s primary residence as indicated by the parent). There are no restrictions placed on family type (eg, single parent, shared parenting and inclusion of extended family living in the main household) and no maximum number of participants per family. All participants need to be able to perform light-intensity PA (eg, walking), have access to the Internet and understand the English language sufficiently well to provide informed consent. Family members are able to take part in the intervention irrespective of their participation in the accompanying evaluation and vice versa. Exclusion criteria related to participation in specific assessments are outlined below with the outcome measures.

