### Sample size considerations

Since this is a pilot study, a sample size calculation will not be performed. We plan to recruit a sample of 60 families, with a sample size of ~180–240 participants based on ~3–4 members per family. Our estimated sample size is based on prior study experience^31^ and sample sizes of previous pilot studies.^58 59^

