### Data analysis

#### Quantitative data

Statistical analyses of the primary and applicable secondary outcomes will be conducted using linear mixed models in Stata V.14. The models will be used to assess the impact of treatment (FRESH, pedometer-only or control), time, (baseline, 8 weeks and 52 weeks) and the group-by-time interaction. An estimate of effect and 95% CI will be calculated. Descriptive statistics will also be calculated to describe data related to recruitment, retention, acceptability, family functioning and website engagement.

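### Child BMI is put on the percentile scale, and the planned linear mixed models would then give less weight to change in the children with the highest (and lowest) BMI; z-scores from the same charts would not

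*Protocol article*

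**What the plan says.** Under Secondary outcomes, Health outcomes, the protocol article lists height, weight and waist circumference. It then says that BMI will be calculated and, for children, "converted into age-specific and sex-specific percentiles using standard growth charts for children". No z-score or SD score is mentioned.

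Under Data analysis, Quantitative data, it says: "Statistical analyses of the primary and applicable secondary outcomes will be conducted using linear mixed models in Stata V.14". The model terms are treatment, "time, (baseline, 8 weeks and 52 weeks) and the group-by-time interaction". On reporting: "An estimate of effect and 95% CI will be calculated". The section does not list which secondary outcomes count as applicable, and BMI is not named. Descriptive statistics are assigned to recruitment, retention, acceptability, family functioning and website engagement; BMI is not in that list either.

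The eligibility criteria under Participants set no limit on BMI. The physical requirement is that "All participants need to be able to perform light-intensity PA". Children at the top of the growth chart can therefore enter.

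**The concern.** A linear mixed model reports a mean difference on the scale of the outcome and treats a one-unit difference as worth the same everywhere on that scale. A percentile does not behave like that. It is bounded at 0 and 100 and is the normal distribution function of the z-score, so its slope is steep at the median and almost flat in the tails. Two children who shift by the same amount in z contribute very different numbers of percentile points if one starts near the median and the other near the top of the chart.

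At stake is what the BMI estimate means. If it is to carry information about change in children with high BMI, the percentile scale is poorly suited, because their change is heavily compressed. The pilot aims to explore preliminary effectiveness, and its outcome definitions may be carried into a definitive trial, so the scale is worth settling now.

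**Working it through.** **Plan's own figure.** There is none to reproduce. Sample size considerations says "Since this is a pilot study, a sample size calculation will not be performed", and the article gives no BMI effect, SD or distribution.

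**Inputs.**
- Scale: percentile, from Health outcomes.
- Model: linear mixed model, from Quantitative data (inferred for BMI).
- Relation between the scales: percentile = 100 × Φ(z), where Φ is the standard normal distribution function.
- Assumption: a shift of 0.3 z for illustration, since the article gives none. Shifts of 0.1 to 0.5 z are used below to show the range.

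**Step 1: points lost for a fall of 0.3 z.** Formula: 100 × [Φ(z) − Φ(z − 0.3)].

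| Start z | Start percentile | Calculation | Points | Median ÷ this |
|---|---|---|---|---|
| 0 | 50.0 | 100 × (0.50000 − 0.38209) | 11.8 | 1 |
| 1 | 84.1 | 100 × (0.84134 − 0.75804) | 8.3 | 1.4 |
| 2 | 97.7 | 100 × (0.97725 − 0.95543) | 2.2 | 5.4 |
| 2.5 | 99.4 | 100 × (0.99379 − 0.98610) | 0.77 | 15.3 |

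**Step 2: points gained for a rise of 0.3 z.** Formula: 100 × [Φ(z + 0.3) − Φ(z)]. This gives 11.8 points at z = 0, 6.2 at z = 1, 1.2 at z = 2 and 0.37 at z = 2.5. The ratios to the median child are about 10 at z = 2 and about 32 at z = 2.5. Compression at the top is thus stronger for a rise than for a fall. At the bottom of the scale the picture is the mirror image.

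**Step 3: sensitivity to the assumed shift.** For falls of 0.1 to 0.5 z, a child's change in points as a percentage of the median child's is:
- z = 1.33 (91st percentile): 44% to 58%
- z = 1.645 (95th): 28% to 40%
- z = 2: 15% to 23%
- z = 2.5: 5% to 9%
- z = 3: 1.3% to 2.5%

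The change is weakened at the 91st to 95th percentile and becomes very small only from about the 98th upward.

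**Step 4: contribution to the mean.** Suppose that every child falls by 0.2 z. Under three assumed distributions of child z, the children at z ≥ 2 account for:

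| Assumed mean, SD of z | Share of children | Share of mean percentile change |
|---|---|---|
| 0, 1 | 2.3% | 0.3% |
| 0.3, 1.1 | 6.1% | 0.7% |
| 0.5, 1.2 | 10.6% | 1.2% |

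On the z scale the same fall counts as 0.2 for every child, so each group's share of the effect equals its share of the children.

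**The case against.** **The link to the linear model is inferred.** Health outcomes describes how BMI is expressed, not what is modelled; Quantitative data refers only to applicable secondary outcomes; and the analysis plan is not shown. This stands as a caveat. But the article commits to percentiles and offers no other inferential model for a continuous outcome measured at all three time points. The point challenges a stated choice, not a missing detail.

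**The yardstick is z itself.** The argument takes equal z steps as equivalent and then shows that percentiles are not linear in z. Equal z steps are not shown to be equal relative changes in BMI; that depends on the growth reference, which is not at hand. This is fair, and it limits the claim to change in standing. It does not remove the ceiling and floor of the percentile scale.

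**Stronger readings that the document does not support.**
- A reader might infer that the heaviest children drop out of the estimate. They stay in the model; only their change is compressed, and it comes close to vanishing only from about the 98th percentile.
- A reader might infer a biased comparison between arms. Families are randomised, so starting positions are balanced in expectation. The issue is how change is weighted.
- A reader might quote 10- to 32-fold as the size. Those ratios are for a rise in BMI at the top of the scale. For a fall, the direction of interest for a physical activity intervention at high BMI, they are about 5- and 15-fold.

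**Little depends on it.** The article says that the pilot will not support conclusions on effectiveness. No progression criterion names BMI, the cost-effectiveness analysis rests on MVPA and QALYs, and waist circumference is also measured. This stands, and it keeps the point minor.

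**Conclusion.** The point holds as a minor improvement to a stated choice. If child BMI percentile enters the planned linear mixed models, the group-by-time estimate gives less weight to change at both ends of the scale. For a fall of 0.3 z, the weight relative to a child at the median is about 5-fold lower at z = 2 and about 15-fold lower at z = 2.5.

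This rests on three assumptions: that BMI is among the applicable secondary outcomes, that percentile and z are linked by the normal distribution function, and that shifts of the assumed size are plausible. How much it would alter the trial's own estimate cannot be said, because the article gives no BMI distribution. The practical consequence is small in a pilot where BMI is one of many secondary outcomes.

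**What to change.** In Health outcomes, state that the modelled outcome for children is the age- and sex-specific BMI z-score from the same growth charts, and that percentiles will be used to describe weight status. In Quantitative data, name BMI z-score among the outcomes analysed by the mixed model. If percentiles were only ever meant descriptively, a sentence saying so settles the matter.

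The model itself need not change: baseline is already a level of time with a group-by-time interaction, and nothing here argues for a different handling of baseline.

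The measurements and reference charts stay the same, and no new data are needed. The downside is that z-score units are less familiar to readers than percentiles; descriptive percentiles alongside the estimate would offset this.

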#### Behavioural and psychosocial measures

Behavioural and psychosocial measures will be measured via questionnaires distributed to adults and children (those ≤4 years will not complete questionnaires). The questionnaires can be viewed in online supplementary file. These will include: adult and child screen-time use^42–45^; quality of life^46–49^; family co-participation in PA^45^; PA awareness^50 51^; family social norms for PA^52 53^; family support^52^; children’s and adult’s motivation for PA^54 55^; and children’s perceived autonomy, competence and relatedness.^55^

10.1136/bmjopen-2019-030902.supp1Supplementary data

#### Family functioning

The Fictional Family Holiday paradigm will be used to assess family functioning via family relationships^56^ and connectedness.^57^ In this observational paradigm, each family is asked to spend 10 min planning and discussing a week-long holiday itinerary with an unlimited budget. The video-recorded activity is then transcribed prior to coding family functioning, which is indexed through multiple conversational markers, including ‘power-sharing’ (ie, taking turns); parental elicitation of all family members’ viewpoints; expressions of individuality (eg, suggestions for destinations/activities or disagreements) and connectedness (eg, agreements, questions or initiating compromise)^57^; as well as non-verbal markers, including expressions of amity (eg, laughter and displays of affection) or hostility (eg, sarcasm and anger).

#### Family out-of-pocket expenditure for PA

PA-related expenditure for each family member will be collected via a questionnaire that was developed and refined following our feasibility study.^21^ The questionnaire comprises two questions about expenditure related to membership fees and subscriptions (eg, for sports clubs and fitness centres) and sports equipment (eg, sportswear and gadgets) and is completed by the same adult at each time point for their whole family.

### Process evaluation

A mixed methods process evaluation will be conducted after assessments 8 weeks postbaseline. Using opened-ended and 4-point Likert-scale questions (1=strongly disagree and 4=strongly agree), adults will self-report their overall opinion of FRESH, the intervention components, measurements and suggestions for improvement. Children will also self-report on the described topics, responding to dichotomous ‘yes/no’ questions. In addition, semistructured focus groups will be conducted online on 10/20 FRESH families and 5/20 families from each of the other two arms (ie, pedometer-only and control). Focus groups will focus on families’ experience taking part in the trial, perceived acceptability of individual intervention components, intervention fidelity, challenges/barriers encountered and suggested improvements, as appropriate based on study arm allocation. All focus groups will be transcribed verbatim. We will also explore FRESH families’ engagement with the intervention website (eg, page views and challenges accepted/completed) and aspects of the recruitment process (eg, recruitment duration, resources used and comparisons of recruitment strategies).

### Patient and public involvement

FRESH was developed with substantial input from children and families from the public, which has been described elsewhere.^21^ Since the completion of the FRESH feasibility study, families from the public have been further involved with the optimisation of FRESH in a number of ways. As mentioned in section Recruitment protocol, we sought the involvement of families from the public to develop a recruitment video; these families helped to develop the script and acted in the video, which can be viewed online (www.youtube.com/watch?v=UxUHN1JsjUM). We also asked families to engage with the FRESH website and provide feedback to inform modifications that could be made. Lastly, we have included parents as members on our Study Steering Committee.

### Blinding

Researchers conducting analyses will be blinded to family treatment allocation. Research assistants will not be explicitly told family treatment allocation. However, it will not be possible to conceal treatment allocation from participating families.

### Sample size considerations

Since this is a pilot study, a sample size calculation will not be performed. We plan to recruit a sample of 60 families, with a sample size of ~180–240 participants based on ~3–4 members per family. Our estimated sample size is based on prior study experience^31^ and sample sizes of previous pilot studies.^58 59^

### Data analysis

#### Quantitative data

Statistical analyses of the primary and applicable secondary outcomes will be conducted using linear mixed models in Stata V.14. The models will be used to assess the impact of treatment (FRESH, pedometer-only or control), time, (baseline, 8 weeks and 52 weeks) and the group-by-time interaction. An estimate of effect and 95% CI will be calculated. Descriptive statistics will also be calculated to describe data related to recruitment, retention, acceptability, family functioning and website engagement.

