### Randomisation

Randomisation will occur after baseline assessments and the unit of randomisation will be at the family level (ie, the index child and all participating family members). Families will be randomised in blocks of six by an independent statistician using a computer-generated algorithm produced with Stata V.14 and stratified by county (ie, Norfolk or Suffolk). The random allocation sequence will be implemented via a database created in-house on Microsoft Access by independent data management staff. A study coordinator will use the database after baseline to determine which study arm a family is allocated to. No one directly involved in the evaluation will have access to the allocation code or complete sequence.

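### The stated mixed model leaves baseline means free in each arm; a common baseline mean would give more precise effect estimates at no cost in data

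*Protocol article*

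**What the plan says.** The Quantitative data section fixes the model class: "Statistical analyses of the primary and applicable secondary outcomes will be conducted using linear mixed models in Stata V.14". It then lists the terms: the models assess the "impact of treatment (FRESH, pedometer-only or control), time, (baseline, 8 weeks and 52 weeks) and the group-by-time interaction". The result to be reported is given as "An estimate of effect and 95% CI will be calculated". The section does not say which contrast that estimate is, and it mentions neither a baseline covariate nor a common baseline mean.

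The Randomisation section gives the order of events: "Randomisation will occur after baseline assessments and the unit of randomisation will be at the family level". The Outcome evaluation measures section agrees that baseline data come before allocation.

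On size, Sample size considerations states: "We plan to recruit a sample of 60 families, with a sample size of ~180–240 participants based on ~3–4 members per family". It also states: "Since this is a pilot study, a sample size calculation will not be performed". Allocation is 1:1:1 over three arms.

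**The concern.** When baseline is one of the outcome times and treatment enters as a main effect with a full interaction, the model estimates a separate baseline mean for each arm. The interaction terms then compare arms on change from baseline, so the whole of any observed baseline difference is subtracted from the follow-up difference.

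In this trial a baseline difference between arms can only be chance, because allocation follows measurement. The model therefore spends two parameters on differences known to be zero in expectation. It also removes the full baseline gap where only the fraction r of it predicts the follow-up gap. The result is extra variance in each effect estimate.

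The stake is the width of the reported intervals. Exploring preliminary effectiveness is one of the aims in the Introduction. The Economic analyses section uses a change in MVPA and puts its emphasis on uncertainty, leading to a value of information analysis for the definitive trial. Two progression criteria in the Discussion concern the feasible size of that trial and the expected net gain of sampling. The article does not say that the interval from this model is the input to those steps, so the link is plausible but not stated.

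**Working it through.** **Sample.** About 20 families a month for 3 months (Recruitment) gives 20 × 3 = 60 families. At 1:1:1 that is 60/3 = 20 per arm. With 3 to 4 members each, 60 × 3 = 180 and 60 × 4 = 240 participants. The article's figures are reproduced. There is no power calculation to reproduce.

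**Assumptions.** The correlation r is not in the article, so 0.3, 0.5, 0.7 and 0.9 are tried. Outcome SD is 1 at every time, the correlation is the same between all pairs of times, and there is one value per family with n = 20 per arm.

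**Formulas for one pairwise arm contrast, complete data.**
- Free baseline means (difference in change): variance = 2(1 − r) × 2/n
- Common baseline mean: variance = (1 − r²) × 2/n
- Ratio = (1 − r²) / [2(1 − r)] = (1 + r)/2

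**Complete data.** Exact generalised least squares for 3 arms × 3 times agrees with the formulas:

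| r | Variance, free | Variance, common | Ratio | CI narrower by | Equivalent families per arm (20/ratio) |
|---|---|---|---|---|---|
| 0.3 | 0.140 | 0.091 | 0.65 | 19.4% | 30.8 |
| 0.5 | 0.100 | 0.075 | 0.75 | 13.4% | 26.7 |
| 0.7 | 0.060 | 0.051 | 0.85 | 7.8% | 23.5 |
| 0.9 | 0.020 | 0.019 | 0.95 | 2.5% | 21.1 |

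The narrowing is 1 − √ratio. For r = 0.5, 1 − √0.75 = 0.134.

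**52 weeks with 25% missing.** The Discussion sets 75% retention of index children as a progression criterion, so 15 of 20 per arm are taken as observed at 52 weeks. The same least-squares calculation gives:

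| r | Variance, free | Variance, common | Ratio | CI narrower by |
|---|---|---|---|---|
| 0.3 | 0.1687 | 0.1197 | 0.71 | 15.8% |
| 0.5 | 0.1222 | 0.0972 | 0.80 | 10.8% |
| 0.7 | 0.0741 | 0.0651 | 0.88 | 6.3% |
| 0.9 | 0.0249 | 0.0239 | 0.96 | 2.0% |

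**If the unnamed effect were the raw follow-up difference.** With complete data its standard error is √(2/20) = 0.316 at any r. The common-baseline standard errors are 0.302, 0.274, 0.226 and 0.138 for r = 0.3, 0.5, 0.7 and 0.9. Adjustment is still more precise.

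**Several members per family.** With 3 or 4 members analysed, the ratio (1 + r)/2 still holds if r is read as the correlation of family means. Ratios were 0.71 to 0.82 for the variance components tried.

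**Size of the chance baseline gap between two arms.**
- One value per family: SD = √(2/20) = 0.32 outcome SDs. The gap exceeds 0.3 SD with probability 34%.
- All members, 3.5 per family, assumed within-family ICC 0.1: variance of a family mean = (1 + 2.5 × 0.1)/3.5 = 0.357, so SD = √(0.357 × 2/20) = 0.19 and the probability is 11%.
- The same with ICC 0.5: (1 + 2.5 × 0.5)/3.5 = 0.643, so SD = √(0.643 × 2/20) = 0.25 and the probability is 24%.

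**The case against.** The strongest reply is that the article is a condensed account, names no contrast and lists no covariates. A full analysis plan could add baseline adjustment, and such detail is often left to it. Part of this stands: it cannot be said that the trial will report a difference in change. But the article does fix the model terms. Baseline as an outcome time together with a treatment main effect means free baseline means on the ordinary reading, and the raw follow-up contrast from that model is also less precise than an adjusted one.

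Second, a group-by-time mixed model is standard and its estimate is unbiased under randomisation. This stands in full. A reader might infer that chance imbalance and regression to the mean will bias the results. The documents do not support that. Averaged over randomisations there is no bias. Regression to the mean matters only conditionally on the imbalance that happens to occur, and its cost is the extra variance already counted above.

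Third, the trial is a pilot that disclaims conclusions on effectiveness, and most progression criteria concern recruitment, retention, adherence and acceptability. This also stands and limits the importance of the point.

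Fourth, quoting only complete data and r up to 0.7 would flatter the gain. That is fair, which is why the 52-week figures with missing data and the case r = 0.9 are shown.

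Finally, a reader might treat a model with baseline as a covariate as an equivalent remedy. It is not. The primary outcome needs a valid accelerometer week, so some baselines may be missing. The covariate model drops those participants unless baseline is imputed, while the stated model and the constrained model both keep their follow-up data.

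**Conclusion.** The point holds as one of efficiency. The stated terms leave each arm its own baseline mean although randomisation makes the true means equal, and either natural contrast from that model is less precise than one with a common baseline mean. Against the interaction contrast, the interval narrows by between 19% (r = 0.3) and 2.5% (r = 0.9) with complete data. At 52 weeks with a quarter missing the range is about 16% to 2%. These figures rest on an assumed r, equal variances and equal correlations between times. If r is near 0.9 the gain is negligible; at 0.3 to 0.7 it is worth having. It is not an error of validity, and its importance in a pilot is modest.

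**What to change.** Keep the linear mixed model with baseline, 8 and 52 weeks as outcome times, but constrain the baseline mean to be common to the three arms. In practice, drop the treatment effect at baseline and let arms differ only at 8 and 52 weeks. Name the between-arm differences at 8 and at 52 weeks as the effect estimates to be reported with 95% CIs. Prefer this to a model with baseline as a covariate, for the missing-baseline reason given above.

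The cost is a change of wording in the analysis section. It needs no new data or visits, and the constrained model has two fewer parameters than the one now described.
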